**Background**:

Approximately 8-10 million patients complaining of chest pain present to an Emergency Department (ED) annually in the United States. These patients are a challenge to healthcare providers, who are tasked with determining whether these symptoms are due to an acute coronary syndrome (ACS) or a non-ACS cause. Missing the diagnosis of ACS is associated with high rates of morbidity, mortality, and malpractice claims. Therefore, to avoid missing the diagnosis of ACS, patients with chest pain typically undergo extensive evaluations at an estimated cost of $10-13 billion annually. However, less than 10% of these patients are ultimately diagnosed with ACS. As the US healthcare system shifts towards a value-based model, it is clear that the current care patterns for acute chest pain, which fail to focus health system resources, such as hospitalization and cardiac testing, on patients most likely to benefit, are not sustainable.

In an effort to improve the quality and value of care for patients with acute chest pain, our group recently validated a risk stratification pathway, the HEART Pathway, which is designed to focus cardiac testing and admissions on higher-risk patients, who are more likely to benefit from testing. The HEART Pathway, which utilizes an easy to use clinical decision aid (the HEART score) and serial troponin measurement, has been shown to significantly reduce objective cardiac testing (stress testing and coronary angiography), shorten hospital length of stay, and increase the early discharge rate from the Emergency Department among patients with acute chest pain. These important efficiency gains occur without missing ACS and without increasing return visits to the ED or downstream admissions to the hospital over a 30 day period.

While the HEART score has been well validated in the ED setting, it has yet to be implemented in a prehospital setting. Paramedics are often the first providers to evaluate and begin treating patients with symptoms concerning for ACS. Current pre-hospital risk stratification is largely based on a combination of ECG results and paramedic gestalt. Since ECGs without signs of a STEMI are poor predictors of ACS, paramedics often have difficulty distinguishing high-risk patients from low-risk patients. Therefore, integrating objective risk stratification tools, such as the HEART score and point-of-care troponin testing, into Emergency Medical Services (EMS) triage and destination plans represents an opportunity to improve care. Furthermore, expanding use of the HEART score to paramedics in the pre-hospital setting is a natural extension of our prior work, especially given the growing sophistication of mobile integrated healthcare (“community paramedicine”) over the last decade. Thus, **multidisciplinary leaders within Emergency Medicine, Cardiology, and Prehospital Medicine have agreed that a limited/pilot evaluation of the HEART Score with Abbott’s i-STAT^®^ point-of-care (POC) troponin testing in the prehospital setting is needed.**

We anticipate that a standardized approach to paramedic risk stratification using the HEART score with Abbott’s i-STAT^®^ POC troponin testing will be feasible and achieve high accuracy for the detection of ACS. Ultimately we believe this planned implementation will improve the quality and value of chest pain care. Placing these tools in the hands of our first responders will identify patients with ACS earlier and speed the delivery of potentially life-saving care. For example, EMS triage and destination plans (chest pain treatment and transportation triage and destination plans) could be amended so that patients with positive POC troponins or high HEART scores could be transported directly to a hospital with cardiac catheterization capabilities, avoiding delays and costs associated with inter-facility transfers. However, before EMS triage and destination plans can fully incorporate the HEART score and POC troponin testing, first the feasibility of such an implementation must be established by collecting quality surveillance data.

To establish the feasibility and accuracy of HEART score and POC testing in the prehospital setting we propose a quality surveillance study of a limited implementation of the HEART score with POC troponin testing. This pilot will include paramedics from three demographically distinct counties (Forsyth, Surry, and Stokes counties) in North Carolina, who will begin using the HEART score and i-STAT POC Troponin as part of their risk assessment for patients with acute chest pain. However, EMS triage and transportation plans will not be altered based on the HEART score assessment until feasibility and accuracy have been established. To ensure the feasibility and accuracy of paramedic chest pain risk assessment we will be performing surveillance of electronic health records (EHR) and contacting patients by phone (which is a common practice in EMS quality assurance). The long term goal of this project is to provide data to support a larger scale implementation with greater integration of the HEART score and POC troponin testing into EMS triage and destination plans. Once the feasibility and accuracy are established, we anticipate that the HEART Score and POC troponin measurement will be used to speed the delivery of high-value care to patients with acute chest pain. While this project is a clinical pilot, given our intent to publish the data generated from this implementation, it meets the definition of human subjects research.

**Objective:**

The primary concept of the proposed quality improvement and research program is to assess the feasibility and accuracy of pre-hospital chest pain risk stratification by paramedics using the HEART Score and i-STAT POC troponin assay. In addition, we will determine the agreement and correlation between paramedic and ED physician risk stratification.

**Specific Aims:**

- **Specific Aim 1:** Perform validation (quality control) of the Abbott i-STAT^®^ point-of-care troponin assay in an ambulance; comparing troponin measurements from the patient’s blood samples analyzed in a moving ambulance vs a laboratory setting.
- **Specific Aim 2**: Determine whether paramedics using the HEART score and Abbott’s i-STAT^®^ point-of-care troponin assay in the pre-hospital setting can achieve 98% sensitivity and negative predictive value for major adverse cardiac events (MACE: cardiac death, myocardial infarction, or coronary revascularization) during the index visit and at 30 days in patients with symptoms concerning for ACS.
- **Specific Aim 3:** Test whether the inter-rater reliability (kappa) for risk assessment using the HEART score and Abbott’s i-STAT^®^ point-of-care troponin assay between ED physicians and paramedics exceeds 0.60.
- **Specific Aim 4:** Determine the potential impact of prehospital HEART Score and Abbott i-STAT^®^ point-of-care troponin measurement on the following efficiency outcomes: ED length of stay (LOS), hospitalization rate, and rate of objective cardiac testing (stress testing and coronary angiography).
- **Specific Aim 5**: Determine whether pre-hospital Abbott i-STAT^®^ point-of-care troponins are independent predictors of MACE during index hospitalization and at 30 days in patients with symptoms concerning for ACS.

**Methods:**

To improve the quality of care for patients with acute chest pain within Forsyth, Surry, and Stokes Counties, county EMS medical directors (Drs. [name], [name], and [name]) as well as the EMS Medical Director for the state of North Carolina ([name]) support a pilot implementation of the HEART Score including POC troponin testing beginning in 2016. To ensure the feasibility and safety of this implementation we propose a quality surveillance study. In addition, we have procured funding (Abbott Laboratories) which will support training of paramedics, supply the POC devices, and support the necessary quality surveillance for this implementation.

Over 70 paramedics will be trained to use the Abbott i-STAT device for POC troponin analyses and to calculate a HEART Score. Educational sessions will train the paramedics to correctly identify subjects appropriate for inclusion in the pilot and to correctly calculate a HEART Score. The educational tools will include in-person teaching and may include self-learning modules. Similar teaching methods that have been used in the HEART Pathway Implementation (PI [name]) will be used in these sessions. Training regarding use of the Abbott i-STAT device will be conducted by Abbott Laboratories Inc. trainers. This will include the proper storage, maintenance, and use of device cartridges, quality assurance checks, and the interpretation and reporting or results. Training and competency events will be repeated during the pilot to maintain proficiency.

Following training, we will begin implementation in 18 ambulances across Forsyth County, Surry County, and Stokes County. Quality surveillance participants (n=500) will be identified retrospectively and quality assurance data will be collected electronically using EHR (EMS records, and WFBH health records) and via telephone follow-up calls (which are customary in EMS quality assurance projects). Eligible patients for this pilot implementation will be adult patients, over 21 years old, with non-traumatic chest pain or symptoms concerning for ACS, being transported to WFBMC ED. Patients with acute ST elevation myocardial infarction on initial pre-hospital ECG and patients being transferred from another hospital will be excluded. In addition, patients will be excluded when paramedics estimate that the patient’s pre-hospital time (scene time + transportation time) will be less than 5 minutes.

Paramedics will use a worksheet to obtain the historical and clinical data needed to calculate a HEART score. This will include performing POC troponin testing. This is within the scope of practice of paramedics who routinely perform venipuncture and POC testing on acutely ill patients. Furthermore, the feasibility of performing POC troponin analyses in a moving ambulance has been previously established. Given the paramedic’s need to use the POC troponin value for HEART score calculation they cannot be blinded to the troponin results. However, during this pilot, they will not deviate from their normal chest pain triage and destination plans based on the results. The routine chest pain triage and destination plans for these EMS counties include obtaining an IV, ECG, and the administration of aspirin, nitroglycerin, and supplemental oxygen. Also, during this pilot, i-STAT troponin and HEART Score results will not be used to determine or alter the patient’s transportation destination.

Since paramedics are not blinded to POC troponin results we will not prevent them from sharing their i-STAT troponin results with the ED care team as part of their typical transfer of care reports. However, they will do so using a study specific form, which clearly states that this POC troponin value is for study purposes only and is not to be used to determine a patient’s clinical care. We will train ED nurses and providers that EMS POC troponin results are part of a pilot, should not be acted on clinically at this time, and require confirmation with a core-lab troponin. While the ED care team will receive report on the POC troponin results (as well as the patient’s clinical features and ECG, as part of a normal EMS verbal report), the ED care team will remain blinded to paramedics’ HEART Scores to allow evaluation of agreement between paramedic and ED provider risk assessments. HEART Score calculation by the ED provider is part of the standard ED care for patients with acute chest pain presenting to the WFBMC ED, which will facilitate assessment for agreement. Paramedic POC troponin results and HEART Scores will not become part of the patient’s medical record.

Once participants have been transported to the WFBMC ED, they will receive a standard ED chest pain evaluation, expected to include an ECG and blood draws for troponin measurement. As part of normal care, blood obtained in the ED at presentation and 3 hours following presentation will be used for troponin measurement using the central lab [AccuTnI+3 assay (Beckman Coulter, California) or TnI-Ultra assay (Siemens, Munich Germany)]. In addition, most patients will also receive troponin measurement at presentation and 3 hours with an Abbott i-STAT POC assay.

In EMS quality assurance projects, it is customary for EMS agencies to contact their patients by phone to assess their well-being. Therefore, each patient will be contacted 30-90 days following their pre-hospital encounter to determine if they have had MACE (cardiac death, acute myocardial infarction, and coronary revascularization), hospitalizations, and objective cardiac testing (stress testing and coronary angiography). Patients will also have a record review to determine project outcomes including; MACE, hospitalization, hospital length of stay, and objective cardiac testing.

## A2. Primary Hypotheses

- Paramedics using the HEART score and Abbott’s i-STAT^®^ point-of-care troponin assay in the pre-hospital setting will achieve 98% sensitivity and negative predictive value for MACE during the index visit and at 30 days in patients with symptoms concerning for ACS.
- Inter-rater reliability (kappa) for HEART scores calculated by ED physicians in a hospital setting and paramedics in the pre-hospital setting using Abbott’s i-STAT^®^ point-of-care troponin assay will exceed 0.60.

##

## A3. Purpose of the Project Protocol

The objective of this pilot project is to establish the feasibility and accuracy of prehospital HEART score assessment using an Abbott’s i-STAT^®^ point-of-care troponin assay. If feasibility and accuracy can be established, the HEART score and POC troponin testing will allow modification of triage and destination plans so that patients can be transported to the most appropriate hospital settings as part of a larger implementation evaluation and to speed the delivery of ACS care. For example, patients with positive troponins and high HEART scores could be triaged to facilities with on-site cardiac catheterization laboratories, avoiding costly and inefficient inter-facility transfers. Furthermore, early risk stratification with the HEART Score, is likely to result in downstream efficiency gains; decreasing the ED length of stay for patients with low-risk chest pain.

**B. Background**

B1. Prior Literature and Studies

Coronary heart disease affects 15.8 million people in the US[^1^](#_ENREF_1) and represents a major public health dilemma**.** However, the evaluation process for this disease is inefficient. In the US, patients with symptoms of chest pain are generally evaluated in an ED. As a result, EDs care for 8-10 million patients annually with a complaint of chest pain.[^2^](#_ENREF_2)^,^ [^3^](#_ENREF_3) Of all patients presenting with chest pain, almost two thirds will be admitted to the hospital, but only 10% of these patients are ultimately diagnosed with an acute coronary syndrome (ACS).[^4-7^](#_ENREF_4) This over-triage has been estimated to cost $10-13 billion annually.[^8-10^](#_ENREF_8) Excessive admissions also contribute to hospital and ED crowding, which has been linked to an overall decrease in quality of care.[^11^](#_ENREF_11)^,^ [^12^](#_ENREF_12) This inefficiency also taxes the US in other ways such as lost productivity for affected patients and unnecessary invasive procedures. Equally important, this inefficiency consumes resources that could be diverted for other health interventions.

The evaluation of chest pain is also notoriously difficult for physicians. Despite a high rate of admissions for patients with chest pain, up to 4% of patients with acute myocardial infarction are inappropriately discharged from the ED.[^4^](#_ENREF_4) These patients, inadvertently discharged home with ACS, have higher mortality compared to those hospitalized[^4^](#_ENREF_4), emphasizing the importance of making the correct diagnosis the first time. Thus, physicians have adopted a strategy of admitting most patients with chest pain to observation units or inpatient beds for lengthy evaluations to avoid missing ACS. These practices lead to lengthy hospital stays, exacerbating hospital crowding, and increasing cost.

In response to this issue, a decision aid, called the HEART score was designed to risk stratify patients with chest pain or related symptoms without stress testing or cardiac imaging. It has five

components: History, Electrocardiogram (ECG), Age, Risk factors, and initial Troponin (**Table 1**).[^13^](#_ENREF_13)^,^ [^14^](#_ENREF_14) The HEART Score has been validated in over 5,000 patients, demonstrating a negative predictive value for MACE of 98.3% at 6 weeks.[^13-15^](#_ENREF_13) The HEART Pathway, which includes the HEART Score and serial troponin measurement at 0 and 3 hours increases negative predictive value to >99%.[^16-18^](#_ENREF_16) In a randomized control trial, funded by the American Heart Association, comparing the HEART Pathway to usual care we found that use of the HEART Pathway decreased objective cardiac testing at 30 days by 12.1% (68.8% vs 56.7%, p=0.048), length of stay in the hospital by 12 hours (9.9 vs 21.9 hours, p=0.013), and increased early discharges by 21.3% (39.7% vs 18.4%, p<0.001).

**Table 1.** The HEART score

Low-risk= ≤3, High-risk= ≥4

|  | | Points |
| --- | --- | --- |
| **H**istory | Highly Suspicious | 2 |
|  | Moderately Suspicious | 1 |
|  | Slightly Suspicious | 0 |
| **E**CG | Significant ST-depression | 2 |
|  | Non-specific repolarization abnormality | 1 |
|  | Normal | 0 |
| **A**ge | > 65 | 2 |
|  | 45-64 | 1 |
|  | < 45 | 0 |
| **R**isk factors | 3 or more risk factors | 2 |
|  | 1-2 risk factors | 1 |
|  | No risk factors | 0 |
| **T**roponin | > 3x normal limit | 2 |
|  | 1-3x normal limit | 1 |
|  | < normal limit | 0 |
| Total | |  |

No patients identified for early discharge had major adverse cardiac events at 30 days.[^18^](#_ENREF_18) Based on the results of this trial and the previous studies at WFBMC and in Europe, we have implemented the HEART Pathway at WFBMC. As of November 2014 the HEART Pathway has become the standard chest pain risk stratification tool used in the ED. The PARA-HEART project is a natural extension of our prior work with the HEART Pathway. Pre-hospital utilization of the HEART score has the potential to improve the accuracy of triage, speed care delivery to patients at high-risk of adverse events, and increase the efficiency of their care once they arrive at a medical facility.

## C. Primary Aims

- **Specific Aim 1:** Perform validation (quality control) of the Abbott i-STAT^®^ point-of-care troponin assay in an ambulance; comparing troponin measurements from patient’s blood samples analyzed in a moving ambulance vs a laboratory setting.
- **Specific Aim 2**: Determine whether paramedics using the HEART score and Abbott’s i-STAT^®^ point-of-care troponin assay in the pre-hospital setting can achieve 98% sensitivity and negative predictive value for major adverse cardiac events (MACE: cardiac death, myocardial infarction, or coronary revascularization) during the index visit and at 30 days in patients with symptoms concerning for ACS.
- **Specific Aim 3:** Test whether the inter-rater reliability (kappa) for risk assessment using the HEART score and Abbott’s i-STAT^®^ point-of-care troponin assay between ED physicians and paramedics exceeds 0.60.
- **Specific Aim 4:** Determine the potential impact of prehospital HEART Score and Abbott i-STAT^®^ point-of-care troponin measurement on the following efficiency outcomes: ED length of stay (LOS), hospitalization rate, and rate of objective cardiac testing (stress testing and coronary angiography).
- **Specific Aim 5**: Determine whether pre-hospital Abbott i-STAT^®^ point-of-care troponins are independent predictors of MACE during index hospitalization and at 30 days in patients with symptoms concerning for ACS.

Rationale for the Selection of Outcome Measures

In order for a chest pain risk stratification tool to be considered effective and achieve widespread adoption in the prehospital setting it must accurately detect patients with MACE and there must be high agreement between the paramedics and ED providers. While the HEART Score and troponin testing are well validated for risk stratification in the ED setting, feasibility and accuracy in the prehospital setting have yet to be tested as part of a clinical implementation. Furthermore, the inter-rater reliability (kappa) between paramedics and ED providers has not been tested.

Rationale for 30 day follow-up period

MACE outcomes will be assessed from the index visit through 30 days. ED ACS risk stratification evaluations have traditionally focused on 30 day end-points as recommended in the standardized reporting guidelines for ACS.[^19^](#_ENREF_19)

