*Rationale for not blinding paramedics and ED physicians to POC troponin results*: This is a clinical implementation pilot with a goal of testing the feasibility and accuracy of HEART score assessment using POC troponin results. A troponin result is a required component of the HEART score. Therefore in order to calculate a HEART score paramedics cannot be blinded to POC troponin results. Furthermore, through this implementation project we hope to gain greater understanding of the barriers and facilitators of a real-world implementation of the HEART score and POC troponin testing in a prehospital environment. Therefore, our implementation must closely match the expected paramedic workflow. In addition, we believe that asking unblinded paramedics to not share POC troponin results with receiving ED care team is unethical. In some patients POC troponin testing in the prehospital setting may provide early recognition of an acute myocardial infarction (non-ST-segment elevation myocardial infarction) and medics will be ethically compelled to share this information. However, since the POC troponin results are part of a pilot and their accuracy has not yet been confirmed, the paramedics will share results using a study specific form, which clearly states that this POC troponin value is for study purposes only and is not to be used to determine a patient’s clinical care. We will train ED nurses and providers that EMS POC troponin results are part of a pilot, should not be acted on clinically at this time, and require confirmation with a core-lab troponin. It is important to note that patients will already be receiving standard care for a possible NSTEMI. As part of their existing chest pain triage and destination plans paramedics will already be delivering standard care for acute myocardial infarction (aspirin, supplemental oxygen, and nitroglycerin). ED providers also routinely give patients with chest pain and possible NSTEMI aspirin, supplemental oxygen, nitroglycerin, and in high-risk cases use anticoagulation and antiplatelet therapy.

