In addition to electronic surveillance, follow up phone calls will be used to determine outcomes at 30 days. EMS or project staff will contact each participant at 30-90 days following their pre-hospital encounter using a modified version of a previously described scripted follow-up dialogue[^23^](#_ENREF_23) to further clarify events since discharge, identify events occurring at other care facilities, and to determine health care utilization since discharge. Events of interest will include MACE (cardiac death, acute myocardial infarction, and coronary revascularization), hospitalizations, and objective cardiac testing (stress testing and coronary angiography), and recurrent ED visits. Participants still unable to be contacted will be considered censored at their last known contact unless record review reveals an event occurred, in which case the patient will be considered to have experienced an event. Participants unable to be contacted will be searched for in the Social Security Death Master File. In the event of discrepancy between a participant’s event reporting and the medical record, the medical record will be considered correct.

*Rationale for phone follow up:*  In order to determine the accuracy of paramedic HEART Score assessments for MACE we will need to have a low lost-to-follow-up rate. Without telephone follow-up calls patients who seek follow-up or recurrent care or have adverse events at non-WFBH facilities will not be detected. Furthermore, it is common practice for EMS agencies to use phone follow up to contact patients for quality assurance purposes. Using the above methods we expect to have a lost to follow-up rate less than 10%.

E2. Outcomes

*2a. Primary Outcome*

The primary outcome is MACE at 30 days. MACE is a composite outcome of cardiac death, acute myocardial infarction, and coronary revascularization. MACE occurring in patients with a low-risk HEART score assessment will be considered missed MACE. The primary outcome will be used to determine the sensitivity, negative predictive value, specificity, positive predictive value, likelihood ratios, and accuracy for paramedic detection of MACE at 30 days using the HEART score with i-STAT POC troponin testing.

The definition of cardiovascular death will be based on the Action to Control Cardiovascular Risk in Diabetes (ACCORD) trial.[^24^](#_ENREF_24) Death from stroke will not be considered a cardiac death.

Modified ACCORD definition of Cardiovascular Death:

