1. Unexpected death: Unexpected death presumed to be due to ischemic cardiovascular

disease, occurring within 24 hours of the onset of symptoms without confirmation of

cardiovascular disease, and without clinical or post mortem evidence of other etiology.

2. Fatal Myocardial infarction (MI): death within 7 days of the onset of documented MI

3. Congestive heart failure (CHF): death due to clinical, radiological or postmortem

evidence of CHF without clinical or postmortem evidence of an acute ischemic event

(cardiogenic shock to be included).

4. Death after invasive cardiovascular interventions: death associated with the intervention,

i.e., within 30 days of cardiovascular surgery, or within 7 days of cardiac catheterization,

arrhythmia ablation, angioplasty, atherectomy, stent deployment, or other invasive

coronary or peripheral vascular intervention.

5. Documented arrhythmia: death due to bradyarrhythmias or tachyarrhythmias not

associated with an acute cardiac ischemic event.

6. Death following non-cardiovascular surgery: death due to cardiovascular causes as

defined above within 30 days of surgery.

The definition of myocardial infarction will be based on the recommendations of the 2012 Joint ESC/ACCF/AHA/WHF Task Force for the Redefinition of Myocardial Infarction:[^25^](#_ENREF_25)

A rise and/or fall of troponin with at least 1 value above the 99th percentile of the upper reference limit with at least one of the following: a) symptoms of ischemia, b) ECG changes indicative of new ischemia, c) Development of pathological Q waves on the ECG, d) Imaging evidence of new loss of viable myocardium or new regional wall motion abnormality. Peri-procedural MI is defined in accordance with the most recent 2012 Universal Definition of MI (Types 4a, 4b, and 5).

Coronary revascularization will be defined as angioplasty with or without stent placement, or coronary artery bypass surgery. Coronary revascularization occurring in patients discharged from the ED without objective cardiac testing will be considered missed coronary revascularization.

*2b. Secondary Outcomes*

Objective cardiac testing will be defined by any stress testing modality, coronary CT angiography, or invasive coronary angiography.

Length of stay (LOS) will be the time from ED arrival to hospital discharge for all patients, whether admitted or not.

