*Post-Hoc Analysis of Troponin Cut Points:* For the clinical pilot, paramedics will use a cut point of 0.08 ng/mL, which corresponds to the published 99^th^ percentile upper reference limit for the assay. However, following completion of the pilot we will analyze different troponin cut points (including 0.04 ng/mL) used alone or in combination with the HEART score to find the combination with the greatest accuracy (area under the curve in a receiver operator curve).

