**Validation (Accuracy)**

- - - - 20 QC samples (level 1, 2, and 3) tested in a moving ambulance
- **Will occur concurrently with pilot implementation**

We will compare test samples between i-STAT and the Core Lab troponin method.

i-STAT tested from a FULL lithium heparin green top tube, collected in the field and tested immediately after collection. Blood will NOT be transferred from one collection container to another collection container. The SAME green top tube to be sent to the Core Lab for testing upon arrival to WFBH Emergency Department.

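### Aim 5's composite outcome includes index MI, which is itself troponin-defined, so part of any association with ambulance troponin is built in and index MI should be reported separately

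*Protocol*

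**What the plan says.** Specific Aim 5 (Protocol A1 and C) asks whether pre-hospital i-STAT "point-of-care troponins are independent predictors of MACE during index hospitalization and at 30 days in patients with symptoms concerning for ACS".

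The outcome is fixed elsewhere in the protocol:

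- Components (E2, Primary Outcome): "MACE is a composite outcome of cardiac death, acute myocardial infarction, and coronary revascularization".
- Window (C, rationale for the follow-up period): "MACE outcomes will be assessed from the index visit through 30 days".
- MI (E2): "A rise and/or fall of troponin with at least 1 value above the 99th percentile of the upper reference limit", together with at least one of ischemic symptoms, ECG change, Q waves or imaging evidence.

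On the in-hospital samples, the Methods in A1 say that "blood obtained in the ED at presentation and 3 hours following presentation will be used for troponin measurement". The validation plan in K2 adds, for the ambulance sample: "The SAME green top tube to be sent to the Core Lab for testing upon arrival to WFBH Emergency Department". D4 and its Table 2 describe the same re-test.

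No section separates index MI from later events for Aim 5.

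**The concern.** An independent predictor is normally understood to carry information about an outcome that is established separately from it. For index MI that separation is weak. The outcome needs a raised cardiac troponin, the predictor is a cardiac troponin, and the samples come from the same episode: ambulance, ED arrival and 3 hours later. Because the window opens at the index visit, the same MI counts in both the index-stay and the 30-day result, so the longer window does not remove the overlap.

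What is at stake is interpretation. The pilot is meant to support wider use of point-of-care troponin in EMS triage (A1, A3). A positive Aim 5 result on the composite could be read as added prognostic information when it may show only earlier sight of an MI that the ED would diagnose from its own samples.

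**Working it through.** **1. The plan's own figure.** The protocol gives no number for Aim 5. The only event count is in F2: 50 MACE events at a 10% rate, and 50 / 0.10 = 500 patients. This reproduces. The illustration below uses 50 MACE and 450 non-MACE.

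**2. The overlap, read from the text.**

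| Element | Aim 5 predictor | Index MI as outcome |
|---|---|---|
| Marker | cardiac troponin I, i-STAT (D4, K2) | troponin above the 99th percentile required (E2) |
| Sample | ambulance draw | ED arrival and 3 hours (A1, D4); ambulance tube also run by core lab (D4, K2) |
| Window | start of the episode | counted in both index and 30-day MACE (C) |

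The overlap is real but incomplete. MI also needs a rise and/or fall and a supporting feature, and MACE also includes cardiac death and revascularization.

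**3. How large it could be.** The three inputs are assumptions; the protocol gives none of them:

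- f = share of MACE that is index MI, 0.3 to 0.9
- s = proportion of index MI patients with a positive ambulance troponin, 0.2 to 0.6
- q = proportion positive in everyone else, 0.02 to 0.05

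By construction the ambulance troponin is unrelated to any other MACE. Then:

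- P(positive | MACE) = p = f·s + (1 − f)·q
- crude odds ratio = [p / (1 − p)] / [q / (1 − q)]
- MACE events other than index MI = 50·(1 − f)

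Power is for a two-sided 5% comparison of two proportions, 50 against 450 patients.

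| f | s | q | p | Crude odds ratio, all MACE | Power | Events without index MI |
|---|---|---|---|---|---|---|
| 0.3 | 0.2 | 0.05 | 0.06 + 0.035 = 0.095 | 0.1050 / 0.0526 = 2.0 | 31% | 35 |
| 0.5 | 0.4 | 0.05 | 0.20 + 0.025 = 0.225 | 0.2903 / 0.0526 = 5.5 | 96% | 25 |
| 0.7 | 0.6 | 0.05 | 0.42 + 0.015 = 0.435 | 0.7699 / 0.0526 = 14.6 | about 100% | 15 |
| 0.9 | 0.6 | 0.02 | 0.54 + 0.002 = 0.542 | 1.1834 / 0.0204 = 58.0 | about 100% | 5 |

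The first and last rows are the extremes of the grid. With index MI removed, the odds ratio is 1 in every row. That restates the assumption and is not a result. The table shows only that the composite can give a crude odds ratio of 2 to 58 with no predictive value beyond index MI. The odds ratios are unadjusted.

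**The case against.** The strongest reply is that index MI is the target. D1 and D4 present prehospital troponin as a way to recognise ACS and NSTEMI early, Aim 5 names the index hospitalization openly, and C bases the 30-day endpoint on reporting guidelines. For early detection an association with index MI is expected and legitimate. This stands, and it is why the composite should stay. It does not license the independent-predictor wording for anything beyond index MI.

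A reader might infer several stronger points that the document does not support:

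- **That the association must be strong, or Aim 5 is almost certain to be met.** The odds ratio falls to 2.0 and power to 31% at one end of the assumed range. The assay information in K2 warns that troponin may not appear for 4–6 hours after onset, that different assays are not generally comparable, and that motion can suppress results. Whether one early ambulance value carries signal is a genuine question.
- **That Aim 5 will adjust troponin for a score that already contains it.** D4 does say "A troponin result is a required component of the HEART score", but no section states an Aim 5 model. Covariates may properly sit in an analysis plan that is not shown.
- **That the Aim 5 predictor is split at the 99th percentile.** F3 says "paramedics will use a cut point of 0.08 ng/mL" for the pilot. It does not tie this to Aim 5, and it plans other cut points.
- **That the i-STAT value decides the MI diagnosis.** A1 keeps it out of the medical record. Adjudicators receive the index records (E4), and the ED team is told the result, but no section says that it enters adjudication. The shown problem is a shared marker and episode.

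Replacing the main outcome with MACE other than index MI would also be hard to defend. Events would be few, and part of the link would remain: cardiac death in E2 includes death within 7 days of a documented MI, and revascularization can follow from the index MI diagnosis.

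**Conclusion.** The point holds in a limited form. As fixed in the protocol, the Aim 5 outcome contains a component whose definition requires a raised troponin in the same episode as the predictor. Part of any association is therefore built in, in both windows, and the composite alone cannot establish prediction beyond index MI. This follows from the text of C, E2, D4 and K2 and needs no assumption.

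The size is not known from the document. The crude odds ratio range of about 2 to 58 rests wholly on the assumed f, s and q. Aim 5 is in neither primary hypothesis (A2) and does not drive the sample size (F2), so this calls for a modest change in reporting and wording. The Aim 2 accuracy analysis is not affected.

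**What to change.** Keep the full composite for Aim 5 and add a statement that results will be reported side by side for:

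- (a) index MI, described as early detection;
- (b) MACE other than index MI: MI after the index visit, cardiac death and coronary revascularization.

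Show each component. Use the independent-predictor wording beyond index MI only if (b) supports it. If a HEART-based adjuster is used, take the score without its troponin item (History, ECG, Age, Risk factors).

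The cost is wording and reporting. The worksheet and record data listed in E1, with the outcome adjudication in E4, already supply what is needed. The downside is that (b) will have few events and wide intervals, about 5 to 35 of 50 under the assumed shares. Deaths and revascularizations that follow an index MI stay partly linked to it. Result (b) should be presented as supportive and not as a replacement for the main outcome.
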